## Abstract

**Background:**

Nursing homes are important locations for palliative care. Through comprehensive geriatric assessments (CGAs), evaluations can be made of palliative care needs of nursing home residents. The interRAI Palliative Care instrument (interRAI PC) is a CGA that evaluates diverse palliative care needs of adults in all healthcare settings. The evaluation results in Client Assessment Protocols (CAPs: indications of problems that need addressing) and Scales (e.g. Palliative Index for Mortality (PIM)) which can be used to design, evaluate and adjust care plans. This study aims to examine the effect of using the interRAI PC on the quality of palliative care in nursing homes. Additionally, it aims to evaluate the feasibility and validity of the interRAI PC.

**Methods:**

This study covers phases 0, I and II of the Medical Research Council (MRC) framework for designing and evaluating complex interventions, with a longitudinal, quasi-experimental pretest-posttest design and with mixed methods of evaluation. In phase 0, a systematic literature search is conducted. In phase I, the interRAI PC is adapted for use in Belgium and implemented on the BelRAI-website and a practical training is developed. In phase II, the intervention is tested in fifteen nursing homes. Participating nursing homes fill out the interRAI PC during one year for all residents receiving palliative care. Using a pretest-posttest design with quasi-random assignment to the intervention or control group, the effect of the interRAI PC on the quality of palliative care is evaluated with the Palliative care Outcome Scale (POS). Psychometric analysis is conducted to evaluate the predictive validity of the PIM and the convergent validity of the CAP ‘Mood’ of the interRAI PC. Qualitative data regarding the usability and face validity of the instrument are collected through focus groups, interviews and field notes.

**Discussion:**

This is the first study to evaluate the validity and effect of the interRAI PC in nursing homes, following a methodology based on the MRC framework. This approach improves the study design and implementation and will contribute to a higher generalizability of results. The final result will be a psychometrically evaluated CGA for nursing home residents receiving palliative care.

**Trial registration:**

ClinicalTrials.gov
NCT02281032. Registered October 30th, 2014.

## Background

The population of frail older people dying in nursing homes is rising
[1–3]. In Belgium, the proportion of hospital deaths in people aged 65 and older decreased from 54.3 to 50.5 percent and care home deaths increased from 25.4 to 30.3 percent between 1998 and 2007
[3]. In the United States, 25 percent of the population aged 65 and over dies in a care home
[4]. This percentage is expected to double by 2020
[4, 5]. Subsequently, nursing homes are playing an increasing role in caring for older adults with palliative care needs
[1, 2].

Optimal palliative care in long-term care facilities requires a comprehensive evaluation of the different care needs of nursing home residents
[6, 7]. A comprehensive geriatric assessment (CGA) is defined as ‘a multidimensional, interdisciplinary diagnostic process to determine the medical, psychological and functional capabilities of a frail older person in order to develop a coordinated and integrated plan for treatment and long-term follow-up’
[8]. The main objectives of a CGA are to improve diagnostic accuracy and treatment, optimize functioning and quality of life, extend community tenure, reduce use of unnecessary formal services and improve long-term care management
[8, 9].

In 2005, the multinational consortium interRAI released the interRAI suite of Instruments
[10]. The interRAI suite of instruments contains comprehensive geriatric assessment instruments, developed for different healthcare settings (interRAI Home Care, interRAI Acute Care, interRAI Long-term Care, interRAI Palliative Care, etc.)
[11]. These instruments provide a comprehensive picture of the complex care problems of older people and allow the exchange of data between different care settings
[12]. In Belgium, the interRAI-instruments were translated into Dutch, French and German during the BelRAI project
[13, 14]. Furthermore, the instruments can be linked and filled out on a secured online web-application (belrai.org). Every interRAI-instrument includes a holistic questionnaire about the health condition of the patient and results that are calculated by means of internationally validated algorithms
[15]. Based on these outcomes, care plans can be developed, evaluated and adjusted
[15]. Examples of results are Scales, Quality Indicators (QIs) and Client Assessment Protocols (CAPs).

The interRAI Palliative Care instrument (interRAI PC) was developed as part of the interRAI suite of instruments
[16]. To improve the continuity of care across settings, the interRAI PC is compatible with the other interRAI instruments
[17]. The interRAI PC is a CGA that evaluates the diverse needs and preferences of adults nearing the end of life in all healthcare settings
[16–18]. The aims of the instrument are to improve symptoms, enhance comfort, ameliorate quality of life and assist in coming to terms with death
[18]. Outcomes of the interRAI PC are CAPs and Scales. The CAPs of the interRAI PC instrument are results that inform caregivers to which extent the client’s condition still can improve. The CAPs also inform whether improvement potential is lacking. The goals of care of different CAPs vary and contain the possibility to solve problems, to reduce decline or to create an atmosphere of improvement
[13, 14]. The Scales of the interRAI PC are coherent calculations of client characteristics. These scales are conform to internationally validated scales (Depression Rating Scale, Cognitive Performance Scale, etc.)
[13, 14].

The interRAI suite of instruments is tested and implemented in more than 30 countries and regions worldwide
[10]. Reliability studies on the interRAI PC instrument have already been conducted in six countries
[16, 17]. A systematic review also showed the interRAI PC instrument to be the most comprehensive geriatric assessment instrument that has been partially validated for nursing home residents with palliative care needs
[19]. However, the review also identified that research on the effectiveness and a further validation of the instrument was needed
[19].

This article describes the methods of a phase 0-I-II intervention that was conceived to best address our main research aims:to evaluate the effect of the interRAI PC on the quality of palliative care in nursing homes;to evaluate the feasibility of using the interRAI PC in nursing homes;and to evaluate the face validity of the instrument (as research on the validation of the interRAI PC instrument in nursing homes is deficient).

The study has two additional research objectives:4)to evaluate the predictive validity of the Palliative Index for Mortality (PIM) of the interRAI PC instrument (The PIM predicts the absolute and relative mortality risk within six months. If predictive validity is judged as high this index can internationally be used to detect the need for palliative care [20]);5)to assess the convergent validity of the CAP ‘Mood’ of the interRAI PC instrument. (This CAP refers to depression, sadness and fear. These are psychological characteristics that regularly occur in persons with palliative care needs. These characteristics contribute to a diminished quality of life of the person and his or her family [21]).

The described study protocol will address the following specific research questions:

### Effect

Question 1. Does the use of the interRAI PC instrument improve the quality of spiritual, physical, psychosocial and emotional care for nursing home residents near the end of life?

### Feasibility

Question 2. Is the use of the interRAI PC instrument feasible for care professionals in nursing homes?

### Validity

Question 3. To what extent is the content of the interRAI PC experienced as complete, accurate and clear according to care professionals in nursing homes? (face validity).

Question 4. Is the Palliative Index for Mortality (PIM) of the interRAI PC instrument a good predictor of the risk of mortality within six months of nursing home residents? (predictive validity).

Question 5. Is the Client Assessment Protocol ‘Mood’ of the interRAI PC instrument a valid screening tool for depressive symptoms in nursing home residents with palliative care needs? (convergent validity).

## Methods

### Design of the complex intervention

This research covers phases 0, I and II of the Medical Research Council (MRC) framework for the design and evaluation of complex interventions (Figure 
1)
[22, 23]. The study has a longitudinal, quasi-experimental pretest-posttest design. Mixed methods of evaluation will be used. The intervention will be implemented in fifteen Belgian nursing homes. The multidisciplinary nursing home staff will fill out the interRAI PC for all nursing home residents aged 65 or older with palliative care needs.

**Figure 1 Fig1:**
[figure not shown]
**Study model based on the MRC Framework for designing and evaluating complex interventions.**

#### Phase 0: Preclinical or theoretical

A systematic review was conducted to provide an overview of all existing CGAs that have been validated for nursing home residents with palliative care needs
[19]. Psychometric properties of five identified CGAs have been appraised and their content was evaluated by means of the 13 domains for a palliative approach in residential aged care of the Australian Government Department of Health and Ageing (AGDHA)
[19, 24].

Based on this systematic review, we found that the interRAI PC is the most comprehensive geriatric assessment to evaluate the palliative care needs of nursing home residents. The review also shows that future research should further examine the psychometric properties of the interRAI PC for use in nursing homes
[19].

In the current study, we will take these findings further into practice to evaluate the effect, the feasibility and the validity of the interRAI PC instrument.

#### Phase I: Modeling

During the Modeling phase, the intervention is designed and decisions on what is measured or assessed are made
[22].

The interRAI PC instrument, the manual and the CAPs guidelines were adjusted to two Belgian languages (Dutch and French). Furthermore, the instrument was implemented on the BelRAI web-application (belrai.org).

Additionally, the intervention was designed (Table 
1), taking into account barriers and facilitators of implementing the interRAI-instruments in nursing homes, which have been identified during the BelRAI project
[13, 14]. The main goal of the BelRAI project was to test the interRAI suite of instruments and the BelRAI webapplication in home care, acute care and residential care settings. Barriers and facilitators of implementing the interRAI-instruments in nursing homes have been identified, based on evaluation questionnaires and focus groups with the nursing home staff
[13, 14].

**Table 1 Tab1:** **Description of the intervention**

Preparatory phase		
Steps	Main objective	Secondary objective
Step 0	Introductory information	1. Introduction to the course of the project
		2. Introduction to the interRAI PC instrument
		3. Introduction to the BelRAI webapplication
		4. Identification of the pilot site (avalaibility of computers, laptops, tablets, internet,…)
		5. Capturing important dates (trainings, focus groups,…)
		6. Designation of a contact person
Step 1	Training on the interRAI PC and the BelRAI webapplication	1. One-day training on the interRAI PC and the use of the BelRAI webapplication
		2. Going through the course of the project (planning, questionnaires,…)
Step 2	Introduction on the interRAI PC and the BelRAI webapplication in the organization	1. Establishment of a work group
		2. Introduction of care professionals in the interRAI PC and the use of BelRAI
**Implementation phase**		
**Steps**	**Main objective**	**Secondary objectives**
Step 3	Identification of residents with palliative care needs, based on the surprise question	1. Identification of residents with palliative care needs, based on the surprise question
Step 4	Informed consent signature requirements	1. Designation of a person who is responsible for the informed consents
		2. The assigned responsible explains the project to the residents with palliative care needs or their representatives
		3. Informed consents are signed by the residents with palliative care needs or their representatives
Step 5	Login to the BelRAI webapplication	1. Care professionals apply for acces to the BelRAI webapplication by sending a written solemn declaration to the National Institute for Health and Disability Insurance (NIHDI)
		2. Care professionals login to BelRAI
Step 6	Definitions of roles and functions	1. Based on the profession and diploma of the caregivers, roles and functions are defined in the BelRAI system
		2. The group manager creates a group (the organization or the palliative department) in the BelRAI System
		3. The group manager ads client managers to the group
		4. Client managers create clients in the BelRAI system
		5. Client managers determine who has access to the clients
		6. The assessment manager closes the assessment
Step 7	Completion of the interRAI PC	1. Filling out the interRAI PC for all nursing home residents with palliative care needs
		2. Filling out the interRAI PC on a regular base (every three months)
		3. Multidisciplinary completion of the interRAI PC
Step 8	Interpretation of results	1. Care professionals discuss CAPs and Scales in team/with the patient/with the family
		2. Results are discussed every three months during one year
Step 9	Use of results	1. Results are used to develop a care plan or to adapt an existing care plan

As the introduction of the interRAI PC in clinical practice requires several steps at different stages, a training package for the care professionals of multiple disciplines was developed in order to support the user process of the interRAI PC and the BelRAI web-application.

#### Phase II: Exploratory trial

**General procedures** The effect of the interRAI PC on the quality of palliative care is evaluated, using a pretest-posttest design with quasi-random assignment to the intervention or control nursing homes. Control nursing homes provide care as usual.

**Setting and participants** Calls for participation are sent out by four umbrella organizations of Flemish nursing homes. An announcement is also made during a national conference for nursing home staff.

Fifteen volunteering nursing homes participate in the study. In the course of one year, these participating nursing homes will fill out the interRAI PC every three months for all residents aged 65 years or older with palliative care needs. The need for palliative care is evaluated by means of the surprise question (‘Would you be surprised if this person was to die within 6 to 12 months?’)
[25, 26]. Based on a list of Flemish nursing homes from the National Institute for Health and Disability Insurance (NIHDI), fifteen care homes which match the intervention nursing homes regarding to facility size, ownership and geographic region are contacted for participation in a control group.

**Intervention** The fifteen experimental nursing homes receive the intervention that is being tested. The intervention consists of 11 steps. The complete intervention is described in Table 
1. The fifteen control nursing homes provide care as usual and therefore do not receive the intervention.

**Sample size** Each year, on average 18 percent of the residents in a nursing home in Flanders, Belgium die
[27]. Based on these data, this study aims at including at least 44 nursing home residents with palliative care needs, in order to detect an effect of the use of the interRAI PC instrument on the identified factors. Calculations are based on a medium effect size of 0.50, a two-sided significance level of 0.05 and a power of 0.90 (using G*Power 3.1.5 software)
[28].

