### Outcome measures

#### The effect of the interRAI PC instrument on the quality of palliative care

The multinational consortium interRAI has developed the interRAI PC instrument in order to improve palliative care for elderly
[17]. In order to test this in practice, the effect of the interRAI PC on the quality of palliative care is evaluated.

**Psychometrics** An effect or impact evaluation assesses changes that can be attributed to a particular intervention, such as a project, program or policy, both the intended ones, as well as ideally the unintended ones
[29].

**Data collection** Before the intervention period starts, both experimental and control nursing homes fill out the Palliative care Outcome Scale (POS) for all nursing home residents with palliative care needs. The POS is a ten-item outcome measure that assesses the quality of care in palliative patients
[30]. The instrument contains items on physical, psychosocial and spiritual aspects. There are two versions of the instrument: the POS-Staff version and the POS-Patient version. In this study, we will use the POS-Staff version. The POS can also be used to assess persons with moderate to severe dementia
[31]. The POS is a multidimensional scale that shows good psychometric properties. By means of the POS, the quality of care can be evaluated
[32].

In addition, the experimental and control nursing homes fill out a Retrospective Information (RI) document. This document will provide data on the number of deaths in the past year, the place of death and the availability of a specific palliative care record.

After one year, both experimental and control nursing homes fill out the Palliative care Outcome Scale (POS) and the Retrospective information (RI) document for all nursing home residents with palliative care needs.

**Analysis** Quantitative data are analyzed with SPSS, using independent analysis of covariance (ANCOVA). Research has shown that ANCOVA with pretest-posttest data is the most appropriate statistical procedure in quasi-randomized control-group designs
[33].

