Limitations of the study also need to be acknowledged. Because of time restrictions, the interRAI PC instrument will only be filled out during one year. Therefore, the maximum amount of longitudinal measures is limited to four. Furthermore, the experimental group consists of all nursing home residents with palliative care needs of fifteen nursing homes (public, private, profit and private commercial nursing homes). However, this sample might not be representative of the general Flemish nursing home population. Additionally, due to ethical and practical constraints, participants will not be randomly assigned to the intervention or control group. Because of the strong commitment requirements, nursing homes which volunteer in the experimental group are all included. Moreover, it is impossible to refuse caregivers to fill out the interRAI PC since the instrument is made accessible through the online webapplication BelRAI. Nursing homes are thus included in the experimental group if they are interested in filling out the interRAI PC.

The final result of the study will be a psychometrically evaluated CGA for nursing home residents with palliative care needs, with outcomes that can be used for care planning. If the validity and the effect of the use of the interRAI PC instrument are evaluated positive, this study protocol can form the basis for a larger-scale phase III randomized controlled trial and a broader implementation of the interRAI PC in nursing homes (phase IV). This can further enhance and stimulate optimal palliative care for nursing home residents and eventually also for adults living in other settings. Finally, the international relevance of this study protocol needs to be acknowledged. While the interRAI suite of instruments -and more specifically the interRAI PC instrument- is tested and implemented worldwide, this study protocol can provide guidelines to evaluate the effect, the validity and the usability of interRAI PC in other countries.

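### Allocation is called quasi-random and ANCOVA is justified on that ground, but the intervention homes are self-selected volunteers with matched controls

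*Protocol article*

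**What the plan says.** Two descriptions of how homes enter the groups stand in the protocol article.

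- **Quasi-random.** Phase II: Exploratory trial (General procedures) evaluates the effect "using a pretest-posttest design with quasi-random assignment to the intervention or control nursing homes". The Abstract's Methods paragraph has "Using a pretest-posttest design with quasi-random assignment to the intervention or control group". The analysis paragraph for the effect on quality of palliative care then gives its reason for the method: "Research has shown that ANCOVA with pretest-posttest data is the most appropriate statistical procedure in quasi-randomized control-group designs".
- **By interest.** Under Setting and participants, after open calls, "Fifteen volunteering nursing homes participate in the study", while "fifteen care homes which match the intervention nursing homes regarding to facility size, ownership and geographic region" are approached from a national list to serve as controls. The limitations paragraph of the Discussion says that "participants will not be randomly assigned to the intervention or control group", that "nursing homes which volunteer in the experimental group are all included", and concludes: "Nursing homes are thus included in the experimental group if they are interested in filling out the interRAI PC".

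The Abstract, the design section and the Discussion also call the study quasi-experimental, which is accurate.

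**The concern.** Quasi-experimental and quasi-random are different claims. The first says only that there is a comparison without randomisation. The second says that units were assigned by some rule that stands in for chance. The article makes the second claim and uses it as its stated reason for the analysis of its first-listed aim.

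If interest decides who gets the instrument, motivated homes may differ from controls in palliative care culture, staffing or time trend. Matching on size, ownership and region does not capture motivation. The outcome is the staff version of the POS, filled out by the homes themselves. A reader who takes the label at face value could credit the instrument with a difference that the volunteers brought with them. The article makes a positive result a possible basis for a phase III trial and wider use, so the distinction matters.

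**Working it through.** The plan gives no figure on this point to reproduce. The check compares the texts and then illustrates the size.

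**Step 1: is there an assignment mechanism?** Quasi-random assignment needs a rule outside the homes' own choice, such as alternation, date or list order. The article states none. The intervention group is filled by volunteering, and all volunteers are included. The control group is then built to resemble it on three characteristics. This is a self-selected intervention group with a matched external control group.

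**Step 2: does the analysis rationale depend on the label?** Yes, as worded. The stated reason for ANCOVA is its suitability for quasi-randomised designs, and Step 1 shows that this design is not one.

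**Step 3: what could be left after pretest adjustment?** Inputs:

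- D, the pretest difference between volunteer and control homes in SD of the POS: assumed, 0.2 to 0.5.
- b, the within-group slope of posttest on pretest: assumed, 0.5 to 0.7.
- Planned effect size: 0.50, from the Sample size paragraph. It is read here as a standardised group difference.

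No true effect is assumed, and pretest and posttest scores are taken as linked.

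ANCOVA estimate = posttest difference − b × pretest difference. 
Change-score estimate = posttest difference − pretest difference.

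*Case A, the gap persists in full (posttest difference = D).* ANCOVA leaves D − bD = D(1 − b); the change score leaves D − D = 0.

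| D | ANCOVA, b = 0.5 | ANCOVA, b = 0.7 |
|---|---|---|
| 0.2 | 0.10 | 0.06 |
| 0.3 | 0.15 | 0.09 |
| 0.5 | 0.25 | 0.15 |

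For D = 0.3, the remainder is 0.15/0.50 = 30% to 0.09/0.50 = 18% of the planned effect.

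*Case B, the gap regresses to the mean (posttest difference = bD).* ANCOVA leaves bD − bD = 0. The change score leaves bD − D = −D(1 − b), which for D = 0.3 is −0.15 to −0.09.

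In either case, any extra improvement that volunteer homes would have made without the instrument enters both estimates in full.

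**Step 4: effect on the false-positive rate.** Take a remaining bias of 0.15 SD and b = 0.5, treating the slope as a correlation, ignoring clustering and using the normal approximation. The residual SD is √(1 − 0.25) = 0.866 and the standard error is 0.866 × √(2/n). With 22 residents per arm (44 in total) the standard error is 0.261 and the two-sided 5% test rejects in 8.9% of studies. With 44 per arm the figures are 0.185 and 12.8%. A larger sample does not help, because the bias stays while the standard error shrinks.

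**The case against.** The strongest reply is that nothing is hidden. The Discussion lists the lack of random assignment as a limitation and explains that interest determines entry. The study is called quasi-experimental in several places and is presented as exploratory, with a randomised trial to follow if it succeeds. Controls are matched on three characteristics and a pretest is taken. This stands, and it makes the fault one of label and rationale. It does not remove the fault, because the Abstract and the analysis paragraph still claim the property that the Discussion denies.

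It can also be said that ANCOVA is a legitimate choice for non-equivalent groups. That is correct. A reader might infer that the method is invalid here or that the cited methodological source is wrong. The documents do not support either. The source is not available, and its result may concern non-equivalent groups, with the term used loosely. Only the ground as worded fails.

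A further reading is that a control home which became interested would move to the intervention group. The text does not say so. The sentence about interest explains recruitment, both groups complete the pretest before the intervention starts, and the intervention is a package with training and a work group, not web access alone.

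Finally, the size of any bias is unknown. D and b are assumed, and Case A takes the gap as fully persistent, which is the assumption that favours the change score. The direction is unknown too. This stands: the figures show what is possible, not a bias found in this trial.

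**Conclusion.** The point holds as a contradiction in the text with a consequence for the analysis rationale. Allocation is labelled quasi-random, and ANCOVA is justified on that label, while the article's own account is of self-selected volunteer homes with matched controls. Residual volunteer differences could be read as an intervention effect. It does not follow that they will be, since the limitation is disclosed and no report is at hand.

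Under the assumed stable gap of 0.3 SD and slope of 0.5 to 0.7, ANCOVA would leave 0.15 to 0.09 SD; under regression to the mean it would leave nothing and the change score would be off by the same amount. Nothing in the documents decides between the two. This should be fixed, but given the disclosure and the exploratory purpose it is not a fatal flaw.

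**What to change.** 1. In the Abstract, in Phase II: Exploratory trial and in the analysis paragraph, replace quasi-random and quasi-randomised by: non-randomised, self-selected intervention homes with matched control homes.
2. Remove the present justification of ANCOVA or reword it for a non-equivalent control-group design.
3. Include the matching factors (size, ownership, region) in the ANCOVA. They do not measure motivation, so this does not remove volunteer bias.
4. Report a change-score (difference-in-differences) analysis beside the ANCOVA as a sensitivity analysis, and state its parallel-trends assumption. The two rest on different assumptions, so agreement supports robustness without proving an effect, and disagreement does not show which is wrong. A rule that both must agree before an effect is claimed is not proposed.
5. Describe the result as an association that may include volunteer effects.

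The cost is a few changes of wording, one further analysis of data already planned, some loss of degrees of freedom, and a more modest claim.

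### The minimum of 44 residents is a loss-free analysis number stated as an inclusion number, so it does not support the stated 90% power once deaths before the one-year POS are counted

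*Protocol article*

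**What the plan says.** In the protocol article, under Phase II: Exploratory trial, the sample-size paragraph opens with a mortality figure: "Each year, on average 18 percent of the residents in a nursing home in Flanders, Belgium die". It presents the target as resting on that figure: "this study aims at including at least 44 nursing home residents with palliative care needs, in order to detect an effect". The technical inputs follow: "Calculations are based on a medium effect size of 0.50, a two-sided significance level of 0.05 and a power of 0.90", computed in G*Power. The paragraph mentions no allowance for death, withdrawal or missing forms. It also does not say whether 44 is a total or a number per group.

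The same section fixes who enters. Residents aged 65 or older are identified by the surprise question: "Would you be surprised if this person was to die within 6 to 12 months".

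Under Outcome measures, the effect of the instrument is judged on the Palliative care Outcome Scale (POS), completed before the intervention starts and again a year later in 15 intervention and 15 control homes. The analysis is an ANCOVA, justified there as the suitable method for pretest-posttest data with a control group.

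**The concern.** The target counts residents at entry, while the power depends on residents who can be analysed a year later. In a resident-level ANCOVA with the pretest as covariate, a resident who dies before the second POS contributes nothing. The paragraph names mortality as its starting point, yet the target appears to make no allowance for it. The 18% also describes whole nursing homes, whereas the study enrols residents whose death within a period ending at the posttest would not surprise staff.

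If 44 is read as enough for 90% power, a null POS result could be taken as evidence that the instrument has no effect. The Discussion makes a larger phase III trial depend on a positive evaluation.

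**Working it through.** **Inputs.** From the sample-size paragraph: effect size 0.50 (metric not named), two-sided alpha 0.05, power 0.90, 44 residents included, 18% yearly mortality among all residents. From Outcome measures: posttest at one year. The one-year mortality of residents identified by the surprise question is not given; 30%, 40% and 50% below are assumptions.

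**Step 1: reproduce 44.** For a paired (one-sample) t-test, T has n − 1 degrees of freedom and noncentrality 0.50 × √n. Power is the probability that |T| exceeds the two-sided 5% critical value.
- n = 43: power 0.893
- n = 44: noncentrality 0.50 × √44 = 3.32, power 0.900

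So 44 is the smallest n that reaches 90%, with every resident analysed. An ANCOVA with two groups, one covariate and f = 0.50 comes close (0.899 at 44 in total, 45 needed), but 0.50 is a medium value for d, not for f. That variant has no loss allowance either. The 18% enters neither calculation.

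**Step 2: apply deaths.** Pairs left = 44 × (1 − mortality), rounded down. Inclusion needed to end with 44 pairs = 44 / (1 − mortality), rounded up.

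| One-year mortality | Pairs left from 44 | Power, paired test | Inclusion needed for 44 pairs |
|---|---|---|---|
| 0% (implied by 44) | 44 | 0.900 | 44 |
| 18% (document, all residents) | 44 × 0.82 = 36.1, so 36 | 0.831 | 44 / 0.82 = 53.7, so 54 |
| 30% (assumed) | 30.8, so 30 | 0.754 | 62.9, so 63 |
| 40% (assumed) | 26.4, so 26 | 0.688 | 73.3, so 74 |
| 50% (assumed) | 22 | 0.609 | 88 |

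The ANCOVA with f = 0.50 gives nearly the same: 0.829 with 36 residents, 0.752 with 30, 0.605 with 22. The loss is about 7 points at 18% and 15 to 29 points at 30% to 50%.

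**Step 3: the comparison actually planned.** The analysis compares two groups. For a two-group t-test at d = 0.50, without gain from the covariate and ignoring clustering within homes, 90% power needs 86 residents per group. With no deaths at all, 44 in total (22 + 22) gives 0.367, and 44 per group gives 0.640. Correcting 44 for deaths alone would therefore not give 90% for that comparison. A pretest that correlates with the posttest would raise these figures, but the article states no correlation.

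**The case against.** **44 is a floor.** The text says at least 44, sets no rule to stop there, and has the homes assess all eligible residents. Spread over 30 homes, 44 is about 1.5 residents per home (44 / 30). Actual numbers may be well above it. This stands. It limits the point to the stated minimum and its justification.

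**The same residents may not be measured twice.** The protocol says "After one year, both experimental and control nursing homes fill out the Palliative care Outcome Scale (POS") and the retrospective document, for all residents with palliative care needs; it does not restrict this to residents who had a pretest. With a fresh cross-section at one year, deaths would not reduce the posttest count. This stands as a caveat. But the paired sizing and a resident-level pretest covariate would then not apply, so 44 would lose its basis in another way.

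**The 18% is not called an attrition rate.** It may only indicate how many residents near death the homes can supply. That is fair. It remains the only mortality figure in the document, and on either reading the target contains no allowance for loss.

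**The power figures belong to a one-group test.** This stands too. The 83% shows only that the target fails on the calculation that produced it; it is not the power of the planned comparison.

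**A condensed article may omit an attrition allowance.** The issue here is not an omission. The article prints the number, the inputs and the claimed basis, and these do not fit together.

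**Conclusion.** The point holds for the stated target. The minimum of 44 is a loss-free number analysed, presented as a number included, and the mortality named as its basis does not enter it. On the test that reproduces 44, the document's own 18% takes power from 90% to about 83%. That is a best case: 18% covers all residents, selection by the surprise question should raise mortality, and missing forms or withdrawals would add losses. At assumed mortality of 30% to 50%, power is about 75% to 61%. These figures rest on the same residents supplying both POS scores, which the ANCOVA wording implies but the text does not state.

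A reader might infer two stronger things that the documents do not support. One is that the completed study will be underpowered. That is not shown, because 44 is only a minimum and all eligible residents in the 30 homes are to be scored. The other is that 54 residents, or 83% power, is the figure to print instead. Either would carry a one-group calculation into a two-group design, where 44 falls short of 90% at d = 0.50, without covariate gain, before any death.

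**What to change.** Rewrite the sample-size paragraph in three respects.

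1. Define the target as the number of residents with both a pretest and a one-year POS, and say whether it is a total or per group.
2. Stop presenting 18% as the basis of the number. State the one-year mortality assumed for residents identified by the surprise question, with a range, and derive the expected number of complete pairs from the planned inclusion.
3. Restate the power at that number of pairs for the planned two-group ANCOVA, naming the effect-size metric and the assumed pretest-posttest correlation.

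No recruitment beyond the plan is needed, since all eligible residents are already to be scored, and no procedure changes. The cost is one recalculation, a reworded paragraph and probably a less favourable stated power.
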